## Weekly Treatment Visits (weeks 1-8)

On-treatment study visits (weeks 1, 2, 3, 5, 6, 7) will include directly observed dosing (mDOT) or medication dispensation (unobserved dosing), study drug dosing compliance (pill count), review of concomitant medications and adverse events, urine drug screen, and stored samples for potential testing of SOF and LDV metabolite levels and HCV sequencing, and early termination procedures (if applicable). CBC with diff/CMP and HCV RNA will take place at week 2.

Week 4 visit will include all procedures for weekly study visits as well as symptom-driven physical examination, vital signs, ACASI, HCV RNA, and motivational interviewing for medication adherence.

Week 8 visit will include all procedures for weekly study visits as well as symptom-driven physical examination, vital signs, HCV RNA, CBC with diff/CMP, HCV RNA, HIV Ag/Ab, ACASI, and a qualitative interview.

At each weekly visit, mDOT subjects will receive a 10-trip Muni card to cover weekly round-trip transportation to study site and the unobserved dosing arm will receive a weekly two-trip Muni card to cover round-trip transportation to study site.

Subjects will be compensated $20 for weekly visits 1, 3, 5, 6, and 7; and $25 for the weekly visits with blood draws and/or longer procedures, weeks 2, 4 and 8.

## Early Termination (ET)

For subjects who terminate early, the ET visit will include the same procedures for a standard week 8 visit. Participants will then be asked to complete post-treatment weeks 1, 12 and 36 starting after last dose of the study drug (post-treatment week 1 visit will be 1 week after ET visit).

Gilead (e.g., Medical Monitor and Clinical Program Manager)/CRO will be informed as soon as possible when a subject discontinues treatment.

## Unscheduled Visit

A subject should attend an unscheduled visit if requested by the investigator. The assessments will be as clinically indicated.

## Post Treatment Assessments (post-treatment weeks 1, 12 and 36)

All enrolled subjects will complete the post-treatment weeks 1, 12 and 36 visits, regardless of treatment duration. The post-treatment visits will be scheduled from the date of last administration of study drug, with the exception of the post-treatment week 1 visit, which will be 1 week after week 8 or the ET visit.

Post-treatment week 1 visit will include review of adverse events, provision of end-of-treatment HCV RNA results, and motivational interviewing–based risk reduction counseling.

Post-treatment week 12 and 36 visits will include review of adverse events, urine drug screen, ACASI, HCV RNA, stored samples for potential testing of SOF and LDV metabolite levels, and HCV RNA sequencing.

Subjects will be compensated $15 for post-treatment week 1 visit and $50 for each post-treatment weeks 12 and 36 visits.

## Audio Computer Assisted Self Interview (ACASI)

The ACASI, which is administered at enrollment and weeks 4, 8, and post-treatment weeks 12 and 36, will include injection drug use and injection risk behavior, partner-by-partner data on injection/substance use/HCV status, demographic information (enrollment only), drug use history (enrollment only), quality of life scale (SF-12), Center for Epidemiologic Studies Depression Rating Scale, and Severity of Dependence Scale and participant satisfaction with treatment (week 8 only).

## Assessments for Premature Discontinuation from Study

Discontinuation from study drug dosing and discontinuation from the overall study including follow-up will be collected as two separate events. If a subject discontinues study treatment dosing, every attempt will be made to keep the subject in the study and continue to perform an early termination visit (see Section 6.4) and the required study-related follow-up and procedures (see Section 6.6). This includes post-treatment weeks 1, 12 and 36 visits. If this is not possible or acceptable to the subject or investigator, the subject may be withdrawn from the study.

## End of Study

Subjects are considered to have completed the study after the post-treatment week 36 follow-up visit, regardless of treatment duration and early termination from study drug.

## Procedures and Specifications

### Clinical Laboratory Analytes

Hematology: White Blood Cells (WBC), Red Blood Cells (RBC), Hemoglobin, Hematocrit, MCV, MCH, HCHC, Platelets, with differential, percentages and absolute values, Neutrophils, Lymphocytes, Monocytes, Eosinophils, Basophils, Large Lymphocytes.

Coagulation: Prothrombin time (PT), INR.

Chemistry: Sodium, Potassium, Chloride, Carbon Dioxide, Anion Gap, BUN, Creatinine, eGFR, eGFR African American, Glucose, Total Bilirubin, Total Protein, Albumin, Calcium, Alkaline Phosphatase, AST, ALT.

Virological Tests: Serologies for HCV RNA will be measured using the COBAS^®^ AmpliPrep/COBAS^®^ TaqMan^®^ HCV Quantitative Test, version 2.0. HCV genotype and subtype will be determined using the Siemens VERSANT^®^ HCV Genotype INNO-LiPA 2.0 Assay.

Pregnancy Test: Urine β-hCG

Urine Toxicology: 11 Panel Muti-Drug (Cocaine, Amphetamine, Methamphetamine, THC, Methadone, Opiates, Oxycodone, PCP, Barbituates, Benzodiazepines, and Buprenorphine) Screen Test Card using lateral flow chromatographic immunoassay for the qualitative detection of drugs and drug metabolites at cut-off concentrations that follow guidelines set by the Substance Abuse and Mental Health Services Administration (SAMHSA).

### Medical History

Medical history including details regarding illnesses and allergies, date(s) of onset, and whether condition(s) is currently ongoing, and medication history will be collected on all subjects during screening.

### Complete Physical Examination

A complete physical examination will include source documentation of general appearance, and the following body systems: Head, neck, eyes, ears, nose, throat, mouth and tongue; respiratory; cardiovascular; lymph nodes; abdomen; skin, hair, nails; musculoskeletal; neurological.

### Vital Signs

Vital sign collection will include measurement of resting blood pressure, pulse, respiratory rate, and temperature.

Blood pressure will be measured using the following standardized process:

- Subject will sit with feet flat on the floor and measurement arm supported so that the midpoint of the manometer cuff is at heart level;
- Use a mercury sphygmomanometer or automatic blood pressure device with an appropriately sized cuff with the bladder centered over the brachial artery;
- Measure and record the blood pressure to the nearest 2 mm Hg mark on the manometer or to the nearest whole number on an automatic device.

### Creatinine Clearance

Creatinine clearance is calculated by the Cockcroft-Gault equation [^12^](#_ENREF_12) using actual body weight (BW).

Male: CL_cr_ (mL/min) = [140 - age (years)] × BW(kg)
 72 × S_cr_

Female: CL_cr_ (mL/min) = [140 - age (years)] × BW(kg) × 0.85
 72 × S_cr_

S_cr_ = serum creatinine (mg/dL)

### Body Mass Index (BMI)

BMI is calculated by the following equation.

BMI = weight (pounds) × 703 or weight in kilograms
 (height in inches)^2^ (height in meters)^2^

### The Fibrosis-4 Score (FIB-4):

FIB-4 is calculated by the following equation.

FIB-4 = Age (years) x AST (U/L)

Platelet Count (10 9/L) x √ ALT (U/L)

If FIB-4 <1.45, no or minimal fibrosis, If FIB-4 >3.25, significant fibrosis.

**Excluded from study if FIB-4 >3.25.**

### Fibrosis-Cirrhosis Index (FCI):

FCI is calculated by the following equation.

### FCI = ALP × Bilirubin

### Albumin × Platelet count

### Excluded from study if FCI >1.25.

### Viral RNA Sequencing / Phenotyping Sample

Plasma samples will be collected at screening, weeks 2 and 8, and post-treatment weeks 12 and 36 for potential future HCV viral sequence analysis.

Details regarding the collection, processing, and shipping of samples will be included in the lab manual.

### Pharmacokinetic (PK) Samples

Blood samples will be collected and stored for potential PK testing for all subjects at weeks 2, 4 and 8. PK analysis of SOF (and its metabolites GS‑566500 and GS‑331007) and LDV may be conducted.

Details regarding the collection, processing, and shipping of samples will be included in the lab manual.

### Dried Blood Spot Collection

Dried blood spots will be collected at weekly visits 1, 2, 3, 4, 5, 6, 7, 8 post-treatment weeks 12 and 36, and at the early termination visit (if applicable). The dried blood spots will be stored for potential future testing of SOF and LDV metabolite levels and HCV RNA.

Details regarding the collection, processing and shipment of samples will be included in the lab manual.

### Pregnancy Testing

All females of childbearing potential will have urine pregnancy testing at enrollment. Following enrollment a self-reported positive pregnancy test will be confirmed by urine testing or documentation and the two physicians on the study will review the case to determine if treatment is to be discontinued or continued. This will be decided based on clinical review, incorporating at least the following characteristics: duration of treatment remaining, plans for continuing or terminating pregnancy and severity of liver disease.

### Quality of Life Surveys

The quality of life scale included in this study is the EQ5-D. It will be completed by patients at enrollment, weeks 4 and 8, post-treatment weeks 12 and 36, and early termination (if applicable) regardless of study arm. The Quality of Life Survey will be included in the ACASI.

### Depression Rating Scale

The depression rating scale included in this study is the Center for Epidemiologic Studies Depression Rating Scale. It will be completed by patients at enrollment, weeks 4 and 8, post-treatment weeks 12 and 36 and early termination (if applicable) regardless of study arm. The Depression Rating Scale will be included in the ACASI.

### Severity of Dependence Scale

The Severity of Dependence Scale will be completed by patients at enrollment, weeks 4 and 8, post-treatment weeks 12 and 36 and early termination (if applicable) regardless of study arm. The Severity of Dependence Scale will be included in the ACASI.

# TOXICITY MANAGEMENT

## Subject Stopping Rules

Due to a clinical or laboratory event, administration of study drug may be discontinued. There is no option for LDV/SOF dose reduction. If LDV/SOF is stopped due to toxicity, it must not be restarted, and the subject will complete an ET visit. Post-treatment week 1, 12 and 36 visits will also be scheduled.

Subjects who meet any of the following laboratory criteria must stop study drug:

- Elevation of ALT and/or AST >5x Day 1 or nadir
- Abnormal elevation of ALT >3 x Day 1
- Elevation of ALT >15 x ULN
- Any Grade 3 or greater rash associated with constitutional symptoms
- Any Grade 4 adverse event or laboratory abnormality assessed as related to LDV/SOF

# ADVERSE EVENTS MANAGEMENT

## Definition of Adverse Events, Adverse Reactions, and Serious Adverse Events

### Adverse Event

An adverse event (AE) is any untoward medical occurrence in a clinical study subject administered a pharmaceutical medicinal product, which does not necessarily have a causal relationship with the treatment. An AE can therefore be any unfavorable and/or unintended sign, symptom, or disease temporally associated with the use of a medicinal product, whether or not considered related to the medicinal product. AEs may also include pre- or post‑treatment complications that occur as a result of protocol specified procedures, lack of efficacy, overdose, substance use, or occupational exposure. Preexisting events that increase in severity or change in nature during or as a consequence of participation in the clinical study will also be considered AEs.

An expected adverse event is an AE that may be reasonably anticipated to occur as a result of the study procedures or study participation or is part of the normal disease process or progression.

An unexpected adverse event is defined as being unexpected if the event exceeds the nature, severity, or frequency described in the current Committee on Human Research (CHR) application including the protocol, consent form and investigator brochure, when applicable. An unexpected AE also includes any AE that meets the following criteria:

- Results in subject withdrawal from study participation
- Due to an overdose of study medication
- Due to a deviation from CHR-approved study protocol

An AE does not include the following:

- Medical or surgical procedures (e.g., surgery, endoscopy, tooth extraction, transfusion) performed; the condition that leads to the procedure may be an adverse event and must be reported.
- Pre-existing diseases or conditions or laboratory abnormalities present or detected during or before screening that do not worsen
- Situations where an untoward medical occurrence has not occurred (e.g., hospitalization for elective surgery, social and/or convenience admissions)
- Overdose without clinical sequelae (see Section 8.5)
- Any medical condition or clinically significant laboratory abnormality with an onset date before enrollment and not related to a protocol-associated procedure is not an AE. It is considered to be pre-existing and should be documented on the medical history.
- Substance use or admission to substance use treatment
- Incarceration

### Serious Adverse Events

A **serious adverse event** (SAE) is defined as an event that results in the following:

- Death
- Life-threatening event (Note: The term “life-threatening” in the definition of “serious” refers to an event in which the subject was at risk of death at the time of the event; it does not refer to an event that hypothetically might have caused death if it were more severe.)
- In-patient hospitalization or prolongation of existing hospitalization
- Persistent or significant disability/incapacity
- A congenital anomaly/birth defect or cancer
- A medically important event or reaction: such events may not be immediately life-‑threatening or result in death or hospitalization but may jeopardize the subject or may require intervention to prevent one of the other outcomes constituting SAEs. Medical and scientific judgment must be exercised to determine whether such an event is reportable under expedited reporting rules. Examples of medically important events include intensive treatment in an emergency room or at home for allergic bronchospasm, blood dyscrasias or convulsions that do not result in hospitalization. For the avoidance of doubt, infections resulting from contaminated medicinal product will be considered a medically important event and subject to expedited reporting requirements.
- Event that changes the risk/benefit ratio of the study

### Clinical Laboratory Abnormalities and Other Abnormal Assessments as Adverse Events or Serious Adverse Events

Laboratory abnormalities without clinical significance are not recorded as AEs or SAEs. However, laboratory abnormalities (e.g., clinical chemistry, hematology, and urinalysis) that require medical or surgical intervention or lead to investigational medical product (IMP) interruption, modification, or discontinuation must be recorded as an AE, as well as an SAE, if applicable. In addition, laboratory or other abnormal assessments that are associated with signs and/or symptoms will be recorded as an AE or SAE if they meet the definition of an AE or SAE as described in Sections 8.1.1 and 8.1.2. If the laboratory abnormality is part of a syndrome, record the syndrome or diagnosis (e.g., anemia), not the laboratory result (i.e., decreased hemoglobin).

## Assessment of Adverse Events and Serious Adverse Events

The investigator or qualified sub-investigator is responsible for assessing AEs and SAEs for causality and severity, and for final review and confirmation of accuracy of event information and assessments.

### Assessment of Causality for Study Drug and Procedures

The investigator or qualified sub-investigator is responsible for assessing the relationship to study procedures or medications using clinical judgment and the following considerations:

- **Definitely not**: Evidence exists that the adverse event has an etiology other than the IMP. For SAEs, an alternative causality must be provided (e.g., pre-existing condition, underlying disease, intercurrent illness, or concomitant medication).
- **Probably not**: Adverse event has improbable time relationship to intake of IMP, and attribution with disease or other drugs is likely.
- **Possibly**: Adverse event has reasonable time relationship to intake of IMP, and attribution with disease or other drugs is possible.
- **Probably**: Adverse event has reasonable time relationship to intake of IMP and attribution with disease or other drugs is unlikely.
- **Definitely**: There is reasonable probability that the event may have been caused by the investigational medicinal product.

Ineffective treatment should not be considered as causally related in the context of AE reporting.

The relationship to study procedures (e.g., invasive procedures such as venipuncture) should be assessed using the following considerations:

- **Definitely not**: Evidence exists that the adverse event has an etiology other than the study procedure. For SAEs, an alternative causality must be provided (e.g., pre-existing condition, underlying disease, intercurrent illness, or concomitant medication).
- **Probably not**: Adverse event has improbable time relationship to intake of study procedure, and attribution with disease or other drugs is probable.
- **Possibly**: Adverse event has reasonable time relationship to intake of study procedure and attribution with disease or other drugs is possible.
- **Probably**: Adverse event has reasonable time relationship to intake of study procedure and attribution with disease or other drugs is unlikely.
- **Definitely**: There is reasonable probability that the event may have been caused by the study procedures.

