## Investigator Requirements for Reporting Adverse Events and Serious Adverse Events

### Reporting to UCSF Committee on Human Research (CHR / IRB)

All SAEs and unexpected AEs of relation greater than unrelated must be reported within 5-working-days of PI awareness using the Adverse Event Reporting Form on the UCSF CHR website (iRIS).

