### Reporting to UCLA

Reporting to UCLA Data Safety Monitoring Board (DSMB)

All SAEs and unexpected AEs meeting reportable criteria in the Data Safety Monitoring Plan (DSMP) must be reported within 10-working-days of PI awareness. A summary letter must include detailed accounts of the following:

- Summary of SAE
- Resolution
- Study Drug
- Attribution
- Notification

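### The 'Definitely' level of the causality scale is not defined more strictly than 'Probably', so recorded attribution grades can be inflated or inconsistent

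*Protocol*

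**What the plan says.** Section 8.2.1 asks the investigator to judge the relationship of each event to study drug and to study procedures, "using clinical judgment and the following considerations". Two parallel five-level lists follow. The three upper levels for study drug, taken from the top down, are:

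- *Definitely* asks for one thing only: "There is reasonable probability that the event may have been caused by the investigational medicinal product".
- The level beneath it, *Probably*, sets two conditions: "Adverse event has reasonable time relationship to intake of IMP and attribution with disease or other drugs is unlikely".
- The next one down, *Possibly*, keeps the timing condition and relaxes the other: "Adverse event has reasonable time relationship to intake of IMP, and attribution with disease or other drugs is possible".

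For study procedures, *Definitely* has the same form: "There is reasonable probability that the event may have been caused by the study procedures".

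The rating is used elsewhere. For the safety board, section 8.4 states "A summary letter must include detailed accounts of the following", and attribution is one of the listed items. For the IRB, it states "All SAEs and unexpected AEs of relation greater than unrelated must be reported within 5-working-days of PI awareness". Section 7.1 lists among the mandatory reasons to stop study drug "Any Grade 4 adverse event or laboratory abnormality assessed as related to LDV/SOF". Section 10.1.5 makes causality part of the required source record for every adverse event.

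**The concern.** A graded causality scale works only if each step up demands more evidence than the step below. Here the highest label carries a doubly hedged test (a reasonable probability that the product may have been the cause) and omits the two conditions that define the middle levels. That wording would suit a definition of any related event. It does not describe the most certain category.

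At stake is the meaning of the attribution grade. The participants are actively injecting drugs, so competing explanations for an event will often be present, and this is where an assessor must choose between *Possibly* and something higher. With 30 subjects enrolled and one more planned (section 4.1), a few differently graded events would visibly change any tabulation by causality level.

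**Working it through.** No arithmetic applies, and the protocol gives no figure to reproduce. The check compares the conditions of each level and then traces where the rating is used.

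**Step 1: conditions by level (study drug list).**

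| Level | Timing | Other causes |
|---|---|---|
| Definitely not | not addressed | another cause is evidenced |
| Probably not | improbable | likely |
| Possibly | reasonable | possible |
| Probably | reasonable | unlikely |
| Definitely | not addressed | not addressed; only a reasonable probability of causation |

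From *Probably not* to *Probably* both columns move in the expected direction or hold steady. At *Definitely* both conditions disappear. The procedures list has the same pattern, which argues against a text-extraction fault.

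**Step 2: apply the text to three illustrative events.**

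- Headache in week 1 in a daily heroin user, with plausible timing and another cause possible. It meets *Possibly*. It also meets *Definitely* if the assessor thinks the drug has a reasonable probability of being the cause.
- Fatigue with plausible timing and no other likely cause. It meets *Probably*. An assessor who finds other causes unlikely would ordinarily also accept a reasonable probability of drug causation, so *Definitely* is met as well.
- An event with a clear drug mechanism and every other cause excluded. It meets *Definitely*, on the same sentence that could admit the other two.

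The upper levels are thus neither clearly ordered nor mutually exclusive.

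**Step 3: trace the uses of the rating.**

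- *IRB reporting (8.4)* applies to any relation above unrelated. On an ordinary reading *Possibly*, *Probably* and *Definitely* all qualify, so moving an event among them changes nothing.
- *Safety board and NIH reporting (8.4)*: which events qualify is set by the Data Safety Monitoring Plan, which is not shown. The board's letter does carry the attribution.
- *SAE reporting to the drug supplier (8.4)* is independent of cause or relationship.
- *Stopping rule (7.1)* says related and names no level.
- *Endpoints (9.1)*: none listed uses adverse event causality.
- *Source records (10.1.5)* hold the causality assessment for each event.

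The overlap therefore reaches the recorded grade and the board letter, and no trigger that can be seen.

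**Step 4: the linked vocabulary.** Neither related nor unrelated is a level in 8.2.1, and no mapping is given. In 8.4 the genuine ambiguity is at the lower end: if only *Definitely not* is unrelated, four levels are reportable to the IRB; if *Probably not* is also unrelated, three are. This is separate from the *Definitely* wording.

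**The case against.** The strongest reply is that the labels themselves are plainly ordered, the definitions are offered as considerations alongside clinical judgment, and section 8.2 gives the investigator final review of the assessments. The board also receives a detailed account, so a one-word grade is not all it sees. Nor is a reasonable probability defined: an assessor may decline to treat a merely possible drug cause as reaching it, so the overlap with *Possibly* is likely but not forced for every event. All of this stands. It limits the consequence but does not repair the definition, since a written scale exists to make judgment consistent and here the text works against its own labels.

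A reader might infer more than the protocol supports:

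- *That the attribution sent to the board is wrong.* The text shows that a grade can be ambiguous or inflated; it does not show any incorrect grade.
- *That the top level separates nothing, or that assessors will differ by two levels on the same event.* This requires the most permissive reading of an undefined phrase.
- *That the defect changes IRB reporting or the stopping rule.* No rule shown distinguishes *Definitely* from *Probably* or *Possibly*. It could bear on 7.1 only if related were read to exclude *Possibly*, which the protocol does not say.
- *That 8.4 admits three different cut-points.* Placing the cut at *Probably* would make *Possibly* count as unrelated, which is not a natural reading.

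**Conclusion.** The point holds as a definitional error in section 8.2.1, present in both lists: *Definitely* is not stricter than *Probably*, and an event fitting a lower level may be read as meeting it. The consequence is limited to possible inflation or inconsistency of attribution grades in the adverse event records, in the safety board letter and in any summary by causality level. Its frequency cannot be estimated from the protocol.

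This rests on two assumptions: that assessors use the written definitions as well as the labels, and that the unseen Data Safety Monitoring Plan does not itself turn on the *Definitely* level. If it does, the reach would be wider. The missing mapping of related and unrelated is a real but secondary clarification.

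**What to change.** In section 8.2.1, reword *Definitely* in both lists so that it is stricter than *Probably*: a reasonable time relationship and no other plausible cause (drug or procedure as applicable). Re-check events already rated *Definitely* against the new text.

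Secondarily, state in 8.2.1 which levels count as unrelated for section 8.4, in particular whether *Probably not* does. Section 7.1 also uses a causality term that the scale does not contain; the sponsor should reconcile it with 8.2.1. How that reconciliation is made is a clinical matter and no rule is proposed here.

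The cost is two reworded definitions, a mapping sentence, staff notification, IRB approval before the change takes effect (section 10.2.1) and a short review of past ratings. With thirty subjects already enrolled, much of the benefit is retrospective. Ratings may still be made for the additional subject, and adverse events are reviewed through post-treatment week 36 (section 6.6).
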